### Statistical Analysis

The data will be presented in descriptive basis. The continuous data will be reported by using mean (or median) with standard deviation (or interquartile range). The dichotomous data will be reported using percentage or proportion. Comparing between arms will use student t-test or Wilcoxon Signed Rank Test with a significant level.

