## Objective

### Primary objective

1. To determine if IN can reduce cumulative acute oral mucositis of radiotherapy.

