## Study Design

Prospective, open-label, randomized control trial

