### Randomization

Randomization process will be done at the screening process using central randomization with computer-generated code with block randomization and stratified by radiotherapy centers. Intervention arm will be assigned randomly in 1:1 ratio.

[figure not shown]

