## Statistical Consideration

### Study Endpoint

#### Primary endpoint

1. Difference of the proportion of grade 2-4 CTCEA toxicities of oral mucositis during radiotherapy between IN arm and control arm.

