### Sample size

Based on our previous study on concurrent chemoradiotherapy (CCRT) in nasopharyngeal cancer, incidence of grade  $\geq 2$  oral mucositis according to CTCEA version 3 in CCRT and adjuvant chemotherapy was 61%. The effect of IN on oral mucositis from a metaanalysis by Zheng et al. showed that risk ratio of grade  $\geq 3$  was 0.45 (95% confident interval 0.22–0.92). We assume that IN will half the incidence of oral mucositis to 30.5%. With the power of 0.8 and beta of 0.05, the sample size is calculated to be 41 per arm. With 15% drop out rate is considered, the sample size per arm will be 49.

We will consider rounding up and including 50 participants per arm, the total participants in this study will be 100.

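### The protocol names a paired test for two independent arms and no test for two proportions, although its primary endpoint is a difference in proportions

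*Protocol*

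**What the plan says.** The primary endpoint is "Difference of the proportion of grade 2-4 CTCEA toxicities of oral mucositis during radiotherapy between IN arm and control arm". Both items under Secondary Outcomes are also differences in proportions: the other clinician-graded toxicities, and the patient-reported ones.

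The design is a "Prospective, open-label, randomized control trial" with two arms. On allocation, Randomization says "Intervention arm will be assigned randomly in 1:1 ratio", with "block randomization and stratified by radiotherapy centers". Nothing matches a patient in one arm to a patient in the other.

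On binary data, Statistical Analysis says only "The dichotomous data will be reported using percentage or proportion", which is a rule for description. The next sentence is the only one on testing: "Comparing between arms will use student t-test or Wilcoxon Signed Rank Test with a significant level". It gives no value for the significance level.

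The Sample size section compares 61% with 30.5%, at a power of 0.8 and with a figure of 0.05 that it labels beta, and arrives at 41 per arm.

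**The concern.** The two named tests do not fit the endpoints. The t-test compares means. The signed-rank test ranks within-pair differences, and between two independently randomised arms there are no pairs. To run it, someone would have to pair patients by an arbitrary rule such as row order. If dropout leaves unequal arms, some patients could not be paired at all. The fault reaches the continuous measures too (albumin, weight, blood counts), where the rank-sum test was presumably meant.

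At stake is the primary p-value. In an open-label trial, a choice between two tests, one of them dependent on an arbitrary pairing, should not still be open when the data are seen. Nor is this a detail left for a later document. The protocol makes the choice itself, so an analysis plan that named a chi-square test would contradict it.

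**Working it through.** **1. The test the trial was sized for.** Inputs from Sample size: p1 = 0.61, p2 = 0.305, power 0.8, and 0.05 read as a two-sided alpha. Mean proportion: (0.61 + 0.305)/2 = 0.4575.

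n = [1.960·√(2·0.4575·0.5425) + 0.8416·√(0.61·0.39 + 0.305·0.695)]² / 0.305²
= (1.381 + 0.564)² / 0.0930 = 40.7, so **41 per arm**.

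Dropout: 41/0.85 = 48.2, so **49 per arm**. Both stated figures reproduce. One-sided, the same formula gives 32. The trial was therefore sized for a two-sided test of two independent proportions, which Statistical Analysis does not name. The 0.05 must be alpha, since power 0.8 already fixes beta at 0.20.

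**2. The signed-rank test on 0/1 data.** After arbitrary pairing, each difference is −1, 0 or +1. Zeros drop out and all other ranks are tied, so with b pairs favouring one arm and c the other, the normal-approximation statistic is z = (b − c)/√(b + c). The numerator is fixed by the arm totals. The number of discordant pairs, b + c, depends only on who is paired with whom.

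Illustrative borderline result, 26/42 v 17/42 (b − c = 9). About 42 per arm remain if 15% of 50 drop out (50 × 0.85 = 42.5).

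| Analysis | Two-sided p |
|---|---|
| Chi-square, uncorrected | 0.0495 |
| Student t-test on 0/1 values | 0.0502 |
| Rank-sum | 0.051 |
| Fisher's exact | 0.080 |
| Signed-rank, 11 discordant pairs: z = 9/√11 = 2.71 | 0.007 |
| Signed-rank, 33 discordant pairs: z = 9/√33 = 1.57 | 0.117 |

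The two signed-rank rows are the extremes over 4,000 random pairings. About half of those pairings (49.6%) gave p below 0.05.

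**3. The same test at the planned effect.** 61% v 30.5% is about 26 v 13 of 42, so b − c = 13. The fewest possible discordant pairs is 13 (z = 13/√13 = 3.61, p = 0.0003) and the most is 39 (z = 13/√39 = 2.08, p = 0.037). Every pairing stays below 0.05, against a chi-square p of 0.004.

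**4. What naming the test decides.** Power at 61% v 30.5%, two-sided 0.05, by exact enumeration:

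| Per arm | Chi-square | t-test on 0/1 | Fisher's exact |
|---|---|---|---|
| 41 | 82.5% | 82.5% | 76.0% |
| 42 | 83.9% | 82.4% | 77.8% |
| 50 | 88.7% | 88.7% | 84.2% |

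The t-test option behaves much like chi-square. Fisher's exact test falls below 80% at 41 or 42 evaluable patients per arm.

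**The case against.** The sentence offers the t-test as an alternative. If that is used, the primary p-value is computable and close to chi-square. Its mean difference is the risk difference, with a usable though approximate interval (−0.000 to 0.429 for 26/42 v 17/42, against a Wald interval of 0.005 to 0.423). If the authors meant rank-sum, the answer is again nearly the same. The sample size shows that a comparison of proportions was intended. All of this stands, and it limits the damage to the signed-rank option. It does not make a paired test valid for unpaired arms or supply the missing test.

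The example in the working sits at the edge of significance, and that is also a fair criticism. At the planned effect, no pairing changes the conclusion at 0.05. The range of 0.007 to 0.117 shows what happens to a borderline result and not to a typical one. The protocol does not propose pairing patients at random; it simply gives no pairing at all.

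A reader might also infer that the primary analysis will pool each patient's weekly grades as if independent, since the endpoint is worded in terms of toxicities and the objective is "To determine if IN can reduce cumulative acute oral mucositis of radiotherapy". The documents do not support that. Research Hypothesis speaks of incidence in patients, and Sample size counts each patient once. Nothing in the protocol says that weekly grades will be pooled.

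**Conclusion.** Wrong as written, and to be corrected before analysis. The signed-rank test is invalid for any between-arm comparison in this trial, and no test for two independent proportions is named for a primary endpoint and two secondary outcomes that are all differences in proportions. In a borderline case the signed-rank option can move the primary p-value to either side of 0.05 on pairing alone. The t-test option would cost almost nothing numerically.

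Three stronger conclusions do not follow. The primary p-value is not bound to be arbitrary or incomputable, because that is true only of the signed-rank option. The sample size is not wrong, because 41 and 49 reproduce. No inflated type I error from pooled weekly grades can be charged to this protocol.

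The numbers assume 42 evaluable patients per arm in the examples and the protocol's own 61% and 30.5% in the power figures. The invalidity of the signed-rank test rests on the design alone.

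**What to change.** Replace the testing sentence in Statistical Analysis by:

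> *The primary endpoint (each patient counted once: any grade 2-4 CTCAE oral mucositis during radiotherapy, yes/no) is compared between arms by a two-sided Cochran-Mantel-Haenszel test stratified by radiotherapy centre at alpha 0.05, and reported as a risk difference with 95% CI. The other binary toxicities are analysed the same way. Continuous measures are compared by the independent-samples t-test or, if clearly non-normal, the Wilcoxon rank-sum test.*

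This deletes the signed-rank test, matches the stratified randomisation, and keeps the grade range of the stated endpoint. It also makes the one-value-per-patient reading explicit. In Sample size, relabel the 0.05 as a two-sided alpha. The level is then stated correctly in both places.

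The cost is one paragraph and one corrected word. No extra data, visits or patients are needed, and the planned 50 per arm stands.

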### Interim Analysis

No interim analysis will be performed in this study.

## Sponsor

Thai Otsuka Pharmaceutical Co, Ltd

## Privacy of Patient Data

The collected data will be kept in the cabinet with the lock key or digitally kept in the computer that locks by the password. Only the investigators and regulatory authorities can assess the data.

Volunteer in the study will be coded by using the study-specific number. ID card number, hospital number, name, surname, or the other data that can be identified the identity of the volunteer will not be used or collected in the study.

The data will be retained in the study site for at least 2 years after the final analysis of the study according to ICH/GCH guideline.

